##### Arterial thromboembolism

All 30-day complications perioperative after spinal surgery are recorded. The incidence of all thrombo-embolic events is of interest in order to assess to compare the occurrence between the control and study group. During hospital stay and at regular postoperative outpatient clinical appointments within 6–12 weeks after surgery all perioperative complications are recorded and evaluated in a standardized manner using a case record form. Complications are classified according to a hospital database thesaurus and the severity of the complication is graded (see Table 1).

**Table 1 Tab1:** Grading of complications according to Clavien-Dindo

Grade	Description
1A	Recovery after non-invasive treatment (e.g., medication, physical therapy)
1B	Recovery after invasive treatment (except for operation in an OR) or admission to intensive care
2	Recovery after (re-)operation in an OR
3A	Complication still persists or is treated at the time of registration
3B	Complication resulting in permanent loss of function or disability
4	Death

### Study design

The study is a randomized controlled, non-inferiority trial with two parallel groups. Patients are randomly allocated to either perioperative continuation of aspirin or discontinuation group prior to spinal surgery. Perioperative blood loss, hemorrhage-related complications, need for reoperation events and cardiovascular and/or neuro-embolic events, within 30 days after surgery are evaluated in both treatment groups.

All patients of 18 years and older, referred to the outpatient clinic of the Department of Neurosurgery who are scheduled for elective spinal surgery are eligible for inclusion. The hospitals participating in this study are as follows:Haaglanden Medical CenterHAGA Teaching Hospital Den HaagSpaarne Gasthuis HaarlemAlrijne Hospital Leiderdorp

## Study population

### Population and feasibility

All patients undergoing low complex lumbar spinal surgery in an elective setting using aspirin as antithrombotic therapy.

In the evaluation of the importance of aspirin as an antithrombotic drug and its relevance in its current and future usage, Dutch national statistics show a stable number of 228,000 to 230,000 prescriptions between 2013 and 2017 [4]. In the current cardiologic guidelines in the Netherlands, aspirin forms an important drug in the so-called double platelet therapy in combination with clopidogrel. Studying perioperative continuation and discontinuation of aspirin is relevant and is expected to stay in use.

### Inclusion criteria

In order to be eligible to participate in this study, a subject must meet all of the following criteria:Scheduled low complex lumbar spinal surgery defined as removal of intervertebral disc herniation, decompression of lumbar canal, and/or foraminal stenosis.Preoperative use of aspirinAge >18

### Exclusion criteria

A potential subject who meets any of the following criteria will be excluded from participation in this study:Spinal oncologyStaged surgeries lasting more than one dayPatients with a pre-existing coagulopathy (a proven hemophilia and/or thrombocyte function disorder)Patients using antithrombotic drugs or other platelet aggregation inhibitors than aspirinPatients with absolute contraindications for discontinuing aspirin (e.g., coronary stenting within 1 year)Patients aged under 18Emergency surgical proceduresIncompetence to decide, i.e., in case of severe cognitive impairment or psychiatric illness.

### Sample size calculation

#### Sample size calculation

Because of the research question, the noninferiority of the continuation of aspirin perioperatively in comparison to discontinuation, a noninferiority setup is chosen. Since hemorrhage risk is the main risk of interest in the intervention groups, the sample size calculation is based on these risk percentages. The thrombo-embolic complications are not expected to be raised in the intervention group, as the aspirin functions as a prevention for these events to occur.

The sample size for a noninferiority approach was estimated as *n*=554, *n*=277 per study arm. This was based on the following hemorrhage risk percentages: 1% for the control group, 3% for the intervention group, and 6.1 percentage points as the non-inferiority margin. Calculations were made in PASS Sample Size Software, setting a non-inferiority trial with binary parameters. Below is a summary statement for the sample size estimation.

#### Summary statement

The current practice in Dutch hospitals is to discontinue aspirin pre-operatively. Annual complication registration in our regional database shows a 1% bleeding risk after spinal surgery with the current management. The study by Rahman et al. had a postoperative hematoma rate of 8% versus 4%, with a difference of 4% when not on aspirin perioperatively while Soleman et al. had a 2.5% in postoperative hemorrhagic complications when continuing aspirin [15, 16]. The POISE2-trial presents a hemorrhage risk of 4.6% in patients continuing aspirin in overall surgical patients [5]. These numbers were assumed to not be representative as the studies and the outcome parameters were not comparable to the Aspin study and the study population was not equivalent. Our spinal expert opinion in the Haaglanden Medical Center recommends to maintain a percentage of 3% as a more realistic bleeding risk for the study group.

Sample sizes of 277 in group one and 277 in group two achieve 80% power to detect a

Non-inferiority margin difference between the group proportions of 0.0610. The reference group proportion is 0,0100. The treatment group proportion is assumed to be 0.0710 under the null hypothesis of inferiority. The power was computed for the case when the actual treatment group proportion is 0,.0300. The test statistic used is the one-sided Score test (Miettinen and Nurminen). The significance level of the test was targeted at 0.0250.

## Treatment of subjects

### Investigational product/treatment

#### Standard of care

The group that discontinues aspirin is considered receiving usual care. Currently, all scheduled spinal procedures are performed after discontinuing aspirin for 5 days. After discontinuation of aspirin, coagulation is presumed to have returned to normal because of thrombocyte renewal every 7–10 days. Routinely, no laboratory measurements of blood coagulation are performed to assure this assumption.

Patients who require emergency surgery and thus rapid correction of coagulopathy are excluded from participation.

Aspirin is regularly resumed 3 days after surgery. Exceptions are made at the discretion of the surgeon.

In case of a thrombotic cardiac or neurologic event, perioperative treatment is provided as a conventional matter. Generally, a cardiologist or neurologist is consulted and in close agreement with the surgeon antithrombotic therapy is resumed, and/or other antithrombotic agents are administered.

#### Investigational treatment

The intervention group consists of patients who continue aspirin perioperative. Patient continue their regular dosage of aspirin. The most common indications for the prescription of aspirin are as follows:Primary and secondary prophylaxis of myocardial infarctionPrimary and secondary prophylaxis of stroke (Transient Ischemic Attack and Cerebrovascular Accident)Prevention of vascular graft occlusionPrevention of (hemodialysis) shunt occlusion

The regular dosage for both cardiac and neurologic indications is 80 or 100 mg daily. Patients using antithrombotic drugs or other platelet aggregation inhibitors than aspirin are excluded from the study.

### Use of co-intervention

In this study, all other medications will be continued according to the standard of care. In case the patient uses other anti-thrombotic medication than aspirin, inclusion must not be considered.

In case the study will be extended with the inclusion of patients undergoing spinal lumbar fusion surgery, the following is of interest:

Currently, patients undergoing a spinal spondylodesis with or without posterior lumbar interbody fusion, receive pre-operative 1 g of tranexamic acid on a standard base. This will remain unchanged, considering no bias will occur as patients will be blindly randomized in the control or study group.

### Escape medication

In case aspirin is continued, a potential need for co-interventions exists if hemorrhage-related complications with an indication for reoperation occur. Depending on the severity of the complication and the assessment of the treating physician, thrombocyte transfusion or medication may be administered for rapid correction of coagulopathy.

In case aspirin is discontinued, no co-intervention is to be expected. Patients who require emergency surgery and thus rapid correction of coagulopathy through the administration of platelets or medication are excluded from participation.

Both groups of patients receive venous thromboembolism prophylaxis by means of subcutaneous injections with low molecular weight heparin as standard of care. As this applies to both treatment groups and is not related to the prevention of cardiac and neurologic thrombotic perioperative events, this is not to be considered a relevant co-intervention.

The same management will be maintained in case the study is extended with patients undergoing lumbar spinal fusion. Then the management will be maintained for the administration of tranexamic acid peri-operatively, which is administered per protocol in the posterior lumbar interbody fusion procedures (PLIF). Assuming that patients will be randomly assigned in both study groups, this will remain unchanged.

## Investigational product

Not applicable.

## Non-investigational product

Not applicable.

## Methods

### Primary study outcome: composite of the following bleeding complications

Neurological deterioration as a result of hemorrhage in the surgical area with cauda and/or nerve root compression.Post-surgical anemia with hemoglobin level lower than 5 mmol/l, requiring transfusion.Subcutaneous hematoma leading to wound leakage and pain higher than NRS=7.Major and/or minor hemorrhage in any other body system according to the definition of the International Society on Thrombosis and Haemostasis bleeding scale.Postoperative hemorrhage leading to a clinical indication for re-operation (c.q. evacuation of hematoma).

### Secondary study outcomes

Each of the individual components of the primary outcomeAbsolute mean difference in operative blood loss between the study armsThrombo-embolic-related complications:Myocardial infarctionVenous thromboembolismStrokeArterial thromboembolism

### Primary outcomes: hemorrhage-related complications

#### Neurological deterioration as a result of hemorrhage in the surgical area with cauda and/or nerve root compression

The incidence of 30-day postoperative reoperation incidence is recorded in the hospital information system and recorded with a case record form at discharge from the hospital and during postoperative outpatient clinic visits. Of particular interest are directly hemorrhage-related reoperations. The aforementioned surgical site hemorrhages and postoperative subcutaneous, epidural, or subdural hematomas are infrequent complications of spinal surgery. In case these hemorrhages exert pressure on the surrounding neurologic structures (e.g., spinal cord, cauda equine, nerve roots, or peripheral nerves) a rapid evacuation of the hematoma is required. Furthermore, perioperative hemorrhage-related complications can also result in an indirect need for reoperation. For instance, suboptimal nervous tissue decompression or tumor removal due to excessive bleeding during surgery might result in a need for reoperation. Therefore, the overall 30-day reoperation rate is recorded and compared among both treatment groups.

#### Post-surgical anemia with hemoglobin level lower than 5 mmol/l, needing transfusion

In case of peri- and/or post-operative blood loss leading to symptomatic anemia, objectified with laboratory research, with a hemoglobin level lower than 5 mmol/l a hemoglobin transfusion will be indicated.

Excessive perioperative blood loss can require postoperative allogeneic blood transfusions. The postoperative need for allogenic blood transfusions is registered in the hospital information system and is recorded with a case record form at discharge from the hospital.

The use of autologous blood transfusion is restricted to patients undergoing extensive surgical procedures with high expected blood loss. At the discretion of the surgeon or the anesthesiologist, a cell-saver autologous blood recovery system can be used during surgery. Blood recovered by this system is considered perioperative blood loss. In case a significant amount of blood is recovered and the patient is likely to benefit from an autologous transfusion, autologous blood will be transfused back to the patient.

#### Subcutaneous hematoma leading to wound leakage and pain score

Hemorrhage-related complications include surgical site hemorrhages and postoperative subcutaneous, epidural, or subdural hematomas. Hemorrhage-related complications resulting in an increased length of hospital stay or that require either invasive or non-invasive treatment are recorded in the hospital information system and are recorded with a case record form that is to be filled out at the time of discharge from the hospital and during postoperative outpatient clinic visits. Pain scores will be registered as well, as subcutaneous hematomas can lead to increased discomfort. Pain scores higher than 7 according to the Numeric Rating Scale (NRS) will be registered in the database. Potentially, some complications of spinal surgery can also be indirectly attributed to hemorrhage-related complications. For instance, surgical site hematomas are associated with an increased incidence of postoperative infections. Therefore, the overall 30-day complication rate is recorded and compared among both treatment groups.

#### Hemorrhage in any other body system

Hemorrhage in any other body system within 30 days post-surgery will be noted and compared between groups. These will be classified according to the International Society on Thrombosis and Haemostasis bleeding scale (ISTH-scale) [21].

### Secondary objective

#### All separate primary outcomes individually

##### Absolute mean difference in operative blood loss between the study arms

Perioperative blood loss is determined by measuring blood recovered in the suction device during surgery and weighting of blood-saturated gauzes used during surgery. The Validated Intraoperative Bleeding Scale (VIBe scale) will be used in order to objectify the intraoperative bleeding severity [22]. All cases will receive a vacuum drainage system applied to the surgical wounds in order to record the postoperative blood loss in the first 24 h. Blood loss is registered in the hospital information system and recorded with a case record form that is to be filled out at the time of discharge from the hospital.

##### Thrombo-embolic-related complications

*Myocardial infarction:* myocardial ischemic events diagnosed by a cardiologist according to the fourth universal definition of myocardial infarction.

*Stroke:* diagnosed by a neurologist defined as an acute or transient neurological deterioration with a positive radiological finding for a cerebral ischemic event.

*Venous thromboembolism:* diagnosed by a vascular internist defined as a concordant clinical presentation with a modified Wells score higher than 3, a positive D-dimer level > ng/mL, and a positive ultrasonographical examination.

##### Arterial thromboembolism

All 30-day complications perioperatively after spinal surgery are recorded. The incidence of all thrombo-embolic events is of interest in order to assess to compare the occurrence between the control and study groups. During hospital stay and at regular postoperative outpatient clinical appointment within 6–12 weeks after surgery, all perioperative complications are recorded and evaluated in a standardized manner using a case record form. Complications are classified according to a hospital database thesaurus and the severity of the complication is graded (see Table 1).

### Other study parameters

In order to assess potential confounders additional patient data will be assembled. Body weight, smoking behavior, comorbidities and indication for aspirin prescription, pre-operative use of non-steroid anti-inflammatory drugs (NSAIDs) as analgesic.

Furthermore, the pre- and postoperative satisfaction with the anticoagulant treatment will be assessed by the Anti-Clot Treatment Scale (ACTS). The general health will be assessed pre- and postoperatively by the Patient-Reported Outcomes Measurement Information System (PROMIS Global-10 version 1.2 Dutch) [23, 24].

### Randomization, blinding, and treatment allocation

After evaluation of inclusion and exclusion criteria by the neurosurgeon participants will be randomized by block randomization via Castor EDC. Neither patients of surgeons are blinded to treatment allocation. For practical considerations, patients cannot be blinded to treatment allocation, as they are required to continue or discontinue their aspirin. Surgeons and other treating physicians are not blinded to treatment allocation because the management of potential complications requires knowledge of all current medications. Furthermore, the robust outcome measurements of the study are unlikely affected by knowledge of treatment allocation.

### Study procedures

Patients eligible for inclusion are enrolled at the outpatient clinic. Patients who are scheduled for low-complex lumbar spinal surgery, meeting inclusion and exclusion criteria are informed about the study by their physician. Patients will receive written information on the purpose and the conduction of the study and a consent form. Patients are enabled to carefully read the information on the study after the initial visit. They are allowed to withdraw from the study at any time. Patients who did not give their permission during the initial visit or want to reconsider their decision can contact the research nurse.

Randomization is performed when the operation is scheduled. Regularly, this takes place after pre-surgery evaluation of the patient by the anesthesiologist and time on the potential waiting list prior to surgery. As the standard of care is to discontinue aspirin (and other antithrombotic drugs or other platelet aggregation inhibitors than aspirin) this is at least 1 week prior to surgery.

Study data is recorded with case record forms. After receiving consent from the patient demographic and clinical characteristics are recorded. Outcome measurements are recorded at discharge from the hospital and during the postoperative visit to the outpatient clinic. During this visit, all 30-day postoperative complications will be recorded, that not have been recorded at discharge previously.

No additional visits to the outpatient clinic are required for the purpose of the study.

### Withdrawal of individual subjects

#### Specific criteria for withdrawal

Subjects can leave the study at any time for any reason if they wish to do so without any consequences. The investigator can decide to withdraw a subject from the study for urgent medical reasons.

Patients are removed from the study in case the operation is canceled after a patient has been randomized. Patients who receive new antithrombotic prescriptions in the waiting time to the operation will be withdrawn. Logically, patients who do not follow up on study instructions as consent will be excluded.

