### Follow-up of subjects withdrawn from treatment

No follow-up is different from the normal out-of-study follow-up.

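### Randomised patients are removed for pre-operative events that thrombosis can cause, against the intention-to-treat statement, and thrombo-embolic events are compared only from surgery onward

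*Protocol article*

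**What the plan says.** Two rules under Specific criteria for withdrawal act after randomisation. The first is "Patients are removed from the study in case the operation is canceled after a patient has been randomized". The second is "Patients who receive new antithrombotic prescriptions in the waiting time to the operation will be withdrawn". For patients who leave, the follow-up section says "No follow-up is different from the normal out-of-study follow-up", so the study collects nothing further on them.

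The event window is tied to the operation. Study design says that "need for reoperation events and cardiovascular and/or neuro-embolic events, within 30 days after surgery are evaluated in both treatment groups". The Statistical analysis section uses the same 30-day post-operative period when it compares thrombo-embolic events. Study procedures collects outcomes at discharge and at the post-operative clinic visit.

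The treatment contrast begins earlier. Study procedures randomises when the operation is scheduled. Standard of care says of the control arm that "all scheduled spinal procedures are performed after discontinuing aspirin for 5 days" and that "Aspirin is regularly resumed 3 days after surgery".

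The Statistical analysis section also commits to analysing all randomised patients by intention to treat.

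**The concern.** The allocated difference starts when controls stop aspirin, but the comparison of thrombo-embolic events starts at surgery. An infarction or stroke in the days between lies outside the window. Such an event can plausibly lead to a cancelled operation or a new antithrombotic, and either one triggers removal. Exclusion can then depend on the outcome being studied, which randomisation does not protect against.

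The introduction and the benefit-risk section ask whether extra bleeding outweighs the thrombotic risk of stopping, and the Synthesis section names evidence on thrombo-embolic events as one of the goals. If the pre-operative part of that risk is left out, harm from discontinuation is understated, and so is any benefit of continuation. The outcome is listed as secondary, but its comparison is described under the heading Co-primary study parameter(s).

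**Working it through.** **1. Does this touch the stated sample size?** Inputs from the sample size section: control 1%, intervention 3%, margin 6.1 percentage points, one-sided 0.025, power 80%, Miettinen-Nurminen score test. The score formula with restricted variance under the null gives 275.9, so 276 per arm, against 277 stated. Enumerating the score test at 277 per arm gives power 0.815. The stated figure is reproduced. It rests on bleeding alone, so this point does not change it.

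**2. The passages set side by side.**

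| Step | Place in the protocol | Consequence |
|---|---|---|
| Randomisation when surgery is scheduled | Study procedures | Patient belongs to an arm |
| Control stops aspirin about 5 days before surgery | Standard of care | Arms diverge |
| Infarction or stroke before surgery | Study design; Statistical analysis | Before the window, not compared |
| Operation cancelled, or new antithrombotic started | Specific criteria for withdrawal | Patient removed |
| After removal | Follow-up of subjects withdrawn from treatment | No study follow-up |
| Analysis of all randomised patients | Statistical analysis | Cannot hold together with the removals |

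No section starts the outcome window at randomisation or at aspirin cessation.

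**3. How much off-aspirin time falls before the window?** Days off before surgery: 5. Days off after surgery: 3.

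Share before surgery = 5 / (5 + 3) = 0.625.

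Study procedures also mentions a lead time of at least a week. If that were the length of the stop, the share would be 7 / (7 + 3) = 0.70.

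**4. What could this mean in events?** The protocol gives no thrombo-embolic rates, so the following is illustration only. Assume an excess risk r from stopping, spread evenly over the off-aspirin days, in 277 controls. Expected excess = 277 × r, and the part before surgery = 277 × r × 0.625.

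| Assumed r | Excess events | Before surgery, 5-day stop | Before surgery, 7-day stop (× 0.70) |
|---|---|---|---|
| 0.5% | 1.4 | 0.9 | 1.0 |
| 1% | 2.8 | 1.7 | 1.9 |
| 2% | 5.5 | 3.5 | 3.9 |

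The counts are small, but so is the total from which any contrast would be drawn.

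**The case against.** The strongest reply is that this is a bleeding trial. The primary composite contains only bleeding, the sample size is set on it, and thrombo-embolic events are listed as secondary. The bias described runs against continuation, so it would not flatter the experimental arm. All of that stands, and it limits the weight of the point.

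A reader might infer that 62.5% of the excess events are lost. The document does not support this. The figure counts days and equals a share of events only if excess risk is the same on every off-aspirin day. The protocol itself describes irreversible platelet inhibition and platelet renewal over 7 to 10 days, so the first days off aspirin are probably partly protected and risk would lean towards the counted period. Events after aspirin is resumed, up to day 30, are also counted.

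A reader might also infer that removals are shown to fall mainly on the discontinuation arm. That is plausible on the protocol's premise, but nothing quantifies it. The evidence it cites on thrombotic harm is mixed, and cancellations for unrelated reasons should not differ by arm.

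Nor is it right that pre-operative events must vanish from every record. The adverse event section covers thrombo-embolic complications without a start date, so some may be reported there. They would still not enter the 30-day comparison.

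Finally, the definition of venous thromboembolism, which asks for "a positive ultrasonographical examination", is a separate matter. It applies alike in both arms and is no part of this point.

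**Conclusion.** The point holds in limited form. The removal rules and the intention-to-treat statement contradict each other. The thrombo-embolic comparison omits the pre-operative part of the treatment contrast, and a pre-operative event can cause the patient's own exclusion.

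The direction of the bias, against continuation, rests on two assumptions: that stopping aspirin raises thrombotic risk, as the rationale supposes, and that pre-operative events often lead to cancellation or a new antithrombotic. The only size the document yields is 5 of 8 off-aspirin days. The number of events lost and the imbalance between arms cannot be derived from it. The bleeding primary outcome and the 277 per arm are largely unaffected. The change should be made, but the point does not undermine the trial's main test.

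**What to change.** Reconcile Specific criteria for withdrawal with the intention-to-treat statement in Statistical analysis, and separate leaving the treatment plan from leaving the analysis.

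- Count thrombo-embolic events from randomisation, or from the planned stop date applied equally in both arms, to day 30 after actual surgery, or after the planned date if surgery is cancelled. Starting at randomisation is simplest but includes waiting time in which the arms do not yet differ. The planned stop date avoids that but must be assigned to continuing patients too.
- Keep patients with a cancelled operation or a new antithrombotic in the intention-to-treat set for that outcome, with consent and using routine records.
- Restrict only the surgical bleeding composite to operated patients.
- Report removals by arm and reason.

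No treatment changes and no extra visit is needed. The cost is protocol wording, an event-date item on the case record form, and a procedure for checking the records of the few non-operated patients, who have no discharge or post-operative visit. The consent form already asks about using data after a participant chooses to withdraw. It should be checked that this also covers patients removed under these rules.

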### Replacement of individual subjects after withdrawal

Inclusion will continue until 554 patients in toto are reached, and patients withdrawing consent will be replaced.

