## Statistical analysis

### Co-primary study parameter(s)

Statistical analysis will be performed using SPSS. The risk of hemorrhagic complications and reduction in thrombo-embolic perioperative events within 30 days after surgery will be compared by calculating the confidence intervals of both groups and noninferiority will be claimed if the complication risk percentage stays below 6.1 percentage points.

In order to compare the effect of predefined risk factors on the primary and secondary outcome (Table 2) a multivariate regression model with an intention to treat analysis will be used.

**Table 2 Tab2:** Predefined risk factors

Age	
Sex	
Type of operation Type of spinal procedure: non-instrumented decompression, fusion procedures, spinal level, degenerative, neoplastic	
Duration of surgery	
Amount of preoperative thrombocytes	
Prescribed aspirin dose (80 or 100 mg)	
Previous cardiac or cerebral infarctions (as well as coronary artery disease and transient ischemic attack)	
Duration of surgery	
Type of spinal surgery	

Additional outcomes will be the hemorrhagic outcome measures (perioperative blood loss, hemorrhage-related complications, need for reoperation, and transfusion requirement) that will be compared among both treatment groups with a chi-square or Student’s *t*-test. The treatment group bleeding risk is assumed to be below 0,0710 under the null hypothesis of inferiority.

Follow-up within the study ends at day 30 after surgery. All events after day 30 will not be registered for the Aspin trial. Incidental findings will be registered as well and assigned to the involved organ system.

In case of missing data, patients of the treating surgeon can be contacted to complete the missing information.

All efforts will be made to assemble data for the primary outcome analysis. In case this data is missing, participants will be excluded from the final analysis.

All patients randomized to one of the study arms will be analyzed according to the intention to treat analysis.

Missing data in baseline characteristics will be imputed using multiple imputation (*n*=10) based on the outcome and relevant baseline covariates using the “Multivariate Imputation by Chained Equations” (MICE) algorithm. Patients with missing primary outcomes will be excluded but every effort will be made to obtain follow-up.

The ACTS scale and PROMIS Global-10 score will be compared between pre- and postoperative assessment and between the study and control groups.

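### The protocol promises intention-to-treat analysis of all randomised patients, yet its withdrawal and missing-outcome rules remove some of them, so the primary analysis set contradicts itself and the bias can go either way

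*Protocol article*

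**What the plan says.** In the protocol article, the section Co-primary study parameter(s) states: "All patients randomized to one of the study arms will be analyzed according to the intention to treat analysis". The same section says of missing primary outcome data: "In case this data is missing, participants will be excluded from the final analysis". It then repeats the rule: "Patients with missing primary outcomes will be excluded but every effort will be made to obtain follow-up".

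Specific criteria for withdrawal lists three removals after randomisation:
- cancelled surgery: "Patients are removed from the study in case the operation is canceled after a patient has been randomized"
- a new drug: "Patients who receive new antithrombotic prescriptions in the waiting time to the operation will be withdrawn"
- non-adherence: "Logically, patients who do not follow up on study instructions as consent will be excluded"

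Follow-up of subjects withdrawn from treatment adds: "No follow-up is different from the normal out-of-study follow-up". Under Replacement of individual subjects after withdrawal, recruitment runs to 554 and "patients withdrawing consent will be replaced".

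Neither patients nor surgeons are blinded (Randomization, blinding, and treatment allocation).

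**The concern.** An intention-to-treat analysis of everyone randomised cannot coexist with deleting some of them. Non-adherence, a new prescription, cancellation and loss of follow-up all arise after an allocation that patient and surgeon know. Each could therefore depend on the arm and on perceived or actual bleeding. Replacing consent withdrawals and recruiting to 554 restores the count but not the randomised comparison.

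The choice of set matters because the primary outcome is rare and the test is one of non-inferiority. Dropping patients for reasons linked to bleeding is selection. Keeping patients who took the other arm's treatment pulls the arms together, which favours non-inferiority. As printed, the text does not settle which of these risks the primary analysis runs, and it leaves room to decide once results are known.

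**Working it through.** **1. Inputs from the protocol** (Sample size calculation and Summary statement): control risk 1%, continuation risk 3%, margin 6.1 points, hence 7.1% at the null; one-sided Miettinen-Nurminen score test at 0.025; 277 per arm; 80% power. No rate of non-adherence, exclusion or missing outcome is given, so every such rate below is an assumption.

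**2. The plan's own figure.** Constrained to a difference of 0.061, the maximum-likelihood risks are 0.0673 and 0.0063.
- Standard error under the null: √[(0.0673×0.9327 + 0.0063×0.9937)/277] = 0.01578.
- Standard error under the alternative: √[(0.03×0.97 + 0.01×0.99)/277] = 0.01187.
- Power = Φ[(0.061 − 0.02 − 1.96×0.01578)/0.01187] = Φ(0.848) = 80.2%.

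The smallest n per arm reaching 80% is 276, so the stated 277 reproduces. Exact binomial enumeration at 277 per arm gives power 81.5% and a false non-inferiority rate of 2.05% at 7.1% v 1%. The sample size is not the problem.

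**3. Expected events under the plan.** 277×0.01 = 2.8 and 277×0.03 = 8.3, about 11 in total.

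**4. False non-inferiority rate at the margin, by exact enumeration.**

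*(a) Exclusions unrelated to outcome, not replaced:*

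| Excluded per arm | n per arm | Error | Power (3% v 1%) |
|---|---|---|---|
| 2% | 271 | 2.06% | 80.3% |
| 5% | 263 | 2.01% | 79.3% |
| 10% | 249 | 1.99% | 76.5% |

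*(b) Crossovers in both arms who take on the other arm's full risk.* For crossover share c, the risks under intention to treat are 0.071 − 0.061c and 0.01 + 0.061c.

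| c per arm | Risks if kept | Error if kept | Error if excluded |
|---|---|---|---|
| 5% | 6.80% v 1.31% | 4.6% | about 2.0% |
| 10% | 6.49% v 1.61% | 9.1% | about 2.0% |

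*(c) Exclusion linked to bleeding, continuation arm only, refilled to 277.* At the null that arm has 277×0.071 = 19.7 expected bleeders. If a share f of them is lost, the observed risk is 0.071(1−f)/(1−0.071f).

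| f | Bleeders lost | Observed risk | Error |
|---|---|---|---|
| 10% | about 2 | 6.44% | 4.9% |
| 20% | about 4 | 5.76% | 10.8% |

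If the same share is lost in both arms, the error is 4.3% (10%) or 8.8% (20%).

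**5. Missing outcomes.** With 277 per arm and 3 control events, non-inferiority holds at 11 continuation events (z = −2.00) and fails at 12 (z = −1.77, critical value −1.96). If 3% of an arm were missing, that is 277×0.03 ≈ 8 patients. An observed 3 v 8 would be reversed if 4 of those 8 had bled.

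**The case against.** **The sentence on non-adherence stands under withdrawal.** It does not mention the analysis. The statistical section does so explicitly, but only for missing outcomes. On that reading, non-adherers with data stay in. This is fair: the text does not prove that every non-adherer leaves the analysis. It does not remove the conflict, because withdrawn patients get no study follow-up, an outcome not collected is a missing one, and the missing-outcome rule then deletes them. That rule also conflicts with the intention-to-treat sentence on its own.

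**A reader might infer that the exclusions make a false non-inferiority claim easier.** The figures do not support this as a general statement. Excluding pure crossovers keeps the error near 2%; it is keeping them that raises it. Under exclusion the error rises only if removal is linked to bleeding in the way shown in 4(c). That is plausible in an open-label trial, but nothing in the document shows it. Losing control-arm bleeders alone would push the other way.

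**The missing-data reversal is extreme.** It needs half of the missing patients to have bled. If they bled independently at 3%, the chance of 4 or more in 8 is about 0.005%; at 7.1% it is about 0.14%. The protocol also limits missingness: outcomes are recorded at discharge and at a routine visit, reoperations and transfusions are in the hospital system, and patients can be contacted. So the example shows fragility under informative loss, not a likely result.

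**A per-protocol or missing-data sensitivity analysis may be in the full protocol or analysis plan.** This is accepted. Their absence from the article is not part of the finding. Requiring non-inferiority in both sets would also be a debatable design choice.

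**Conclusion.** The narrower point holds. The protocol defines the primary analysis set in ways that conflict, and applying its exclusions gives a set that is not the randomised one. With about 11 expected events, small numbers matter: about 2 or 4 continuation-arm bleeders lost take the false non-inferiority rate from 2.05% to 4.9% or 10.8%, and 5% or 10% crossover per arm kept under intention to treat alone takes it to 4.6% or 9.1%.

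These figures assume a true difference at the margin, 277 analysed per arm and the stated rates of loss or crossover. The crossover figures also assume that each crossover carries the other arm's full risk. No single direction of bias is established. A separate analysis plan could define the sets properly, but it would still have to override the rules printed here.

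**What to change.** Reconcile the three withdrawal sections with the statistical section:

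1. Delete non-adherence as a reason for exclusion.
2. Collect the day-30 outcome, from the routine visit and hospital records, for every randomised and operated patient who has not refused use of their data, whatever their adherence. The consent form already asks about data use after withdrawal (Recruitment and consent).
3. Analyse these patients as allocated. Name cancelled operations as the one stated exception, and report their number by arm. Patients recruited as replacements add to the set and do not substitute for those withdrawn.
4. Report a per-protocol analysis, defined by actual aspirin intake, alongside the primary one, and interpret non-inferiority in the light of both.
5. Replace deletion for a missing primary outcome with multiple imputation, which is already planned for baseline data, and add a sensitivity analysis that counts missing continuation patients as events.

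The cost is changed wording and a little more analysis. No extra visits are needed. The change concerns data collection and analysis only, not how any patient is treated.
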